## Abstract

**Background:**

Cervical cancer is the leading cause of cancer incidence and mortality among Malawian women, despite being a largely preventable disease. Implementing a cervical cancer screening and preventive treatment (CCSPT) program that utilizes rapid human papillomavirus (HPV) testing on self-collected cervicovaginal samples for screening and thermal ablation for treatment may achieve greater coverage than current programs that use visual inspection with acetic acid (VIA) for screening and cryotherapy for treatment. Furthermore, self-sampling creates the opportunity for community-based screening to increase uptake in populations with low screening rates. Malawi’s public health system utilizes regularly scheduled outreach and village-based clinics to provide routine health services like family planning. Cancer screening is not yet included in these community services. Incorporating self-sampled HPV testing into national policy could address cervical cancer screening barriers in Malawi, though at present the effectiveness, acceptability, appropriateness, feasibility, and cost-effectiveness still need to be demonstrated.

**Methods:**

We designed a cluster randomized feasibility trial to determine the effectiveness, acceptability, appropriateness, feasibility, and budget impact of two models for integrating a HPV-based CCSPT program into family planning (FP) services in Malawi: model 1 involves only clinic-based self-sampled HPV testing, whereas model 2 includes both clinic-based and community-based self-sampled HPV testing. Our algorithm involves self-collection of samples for HPV GeneXpert® testing, visual inspection with acetic acid for HPV-positive women to determine ablative treatment eligibility, and same-day thermal ablation for treatment-eligible women. Interventions will be implemented at 14 selected facilities. Our primary outcome will be the uptake of cervical cancer screening and family planning services during the 18 months of implementation, which will be measured through an Endline Household Survey. We will also conduct mixed methods assessments to understand the acceptability, appropriateness, and feasibility of the interventions, and a cost analysis to assess budget impact.

**Discussion:**

Our trial will provide in-depth information on the implementation of clinic-only and clinic-and-community models for integrating self-sampled HPV testing CCSPT with FP services in Malawi. Findings will provide valuable insight for policymakers and implementers in Malawi and other resource-limited settings with high cervical cancer burden.

**Trial registration:**

ClinicalTrials.gov identifier: NCT04286243. Registered on February 26, 2020.

## Background

Cervical cancer is largely preventable through screening and preventive treatment (CCSPT), yet it remains the leading cause of cancer cases and cancer deaths among Malawian women [1]. Resource-limited countries bear a disproportionate share of global cervical cancer burden: incidence and mortality are two to four times higher in resource-limited countries compared with the highest-resource countries [2]. However, innovative methods for screening and treatment offer increased opportunities to scale-up CCSPT in resource-limited countries.

Malawi introduced a national CCSPT program in 2004 to work towards a national screening rate of 80%, but its reach has been limited. As of 2015, only 26.5% of women had been screened at least once in their lifetime, and only 43% who screened positive received appropriate treatment [3]. The currently used primary screening strategy (visual inspection with acetic acid or VIA) requires a time-consuming pelvic examination, which is challenging to offer for large scale screening because of limited clinic space at health facilities and limited numbers of providers. Timely preventive treatment of screen-positive women is also difficult to achieve because cryotherapy, the currently used ablative treatment, requires relatively expensive and heavy refrigerant gas cylinders [3]. Many of these barriers apply in other resource-limited settings beyond Malawi.

Since the implementation of Malawi’s CCSPT program, the World Health Organization (WHO) now recommends human papillomavirus (HPV)-based screen-and-treat programs where feasible [4]. HPV assays have improved sensitivity over VIA, although with somewhat lower specificity for the detection of high-grade cervical dysplasia [5, 6]. Newer HPV assays allow for results within hours and perform similarly whether a self-collected or provider-collected cervicovaginal sample is used. Self-sampling can remove key bottlenecks for screening because it eliminates the need for a provider and an examination table for initial screening and may be more acceptable to women than physician sampling [7]. A meta-analysis of 34 studies showed that offering self-sampling increased screening uptake compared to standard-of-care, though most of the studies were from high-resource countries [8]. HPV viral DNA remains stable on dry cervicovaginal swabs up to a month after collection [9, 10], which allows delayed testing of self-collected samples and opens up the opportunity for community-based screening, which is especially important for women in rural areas.

Meanwhile, thermal ablation provides a less resource-intensive method for treating screen-positive women. Similar to cryotherapy, thermal ablation is simple to learn and can be performed by mid-level providers, but it does not require heavy gas cylinders and is available through hand-held portable devices. Early experience suggests that thermal ablation has high cure rates, similar to cryotherapy and loop electrosurgical excisional procedures (LEEP) [11, 12]. Some facilities in Malawi have already pivoted to using thermal ablation due to the difficulties with maintaining functioning cryotherapy machines [3, 13].

Introducing a screen-and-treat strategy that combines these innovations—self-sampling, rapid HPV assays, and thermal ablation—promises to improve screening and treatment rates in resource-limited settings including Malawi. However, success requires considering key implementation questions around how to target healthy women and how to reach rural women who have poor access to health facilities. Integrating cervical cancer screening with family planning (FP) services is a promising strategy because many women who access FP services are in the appropriate screening age range and sexually-active. Existing structures to deliver community-based FP services can be utilized to reach women in rural and isolated areas. Any solution for increasing CCSPT services in sub-Saharan Africa must be applicable to rural populations, since an estimated 60–75% of women who develop cervical cancer in sub-Saharan Africa live in rural areas [14].

In many countries, community health workers provide a vital link between health facilities and rural populations. Community-based FP services have been effective in increasing FP uptake in many countries [15], including in Malawi where 80% of the population is rural [16, 17]. Community health workers in Malawi, known as health surveillance assistants (HSAs), provide FP services to rural women through outreach and village clinics. Experience from other countries suggests that community health workers like HSAs can be successfully trained to offer self-sampling for HPV screening in rural areas [18, 19]. However, providing community-based screening introduces additional challenges for follow-up given that same-day screening and treatment will not be conducted. Understanding the impact of community-based screening on loss to follow-up is important given that one of the primary shortcomings in Malawi’s CCSPT program has been the low rate of treatment among screen-positive women. Thermal ablation may be more scalable than cryoablation but would only improve access if women are successfully informed of their results and linked to care at facilities.

We designed a cluster randomized trial to evaluate the effectiveness, acceptability, appropriateness, feasibility, and cost impact of two implementation models. In model 1 (clinic-only), self-sampling will be offered to eligible women attending visits at health facilities (especially targeting those attending FP visits), with same-day thermal ablation for HPV-positive, ablation-eligible women. In model 2 (clinic + community), the same screen-and-treat algorithm will be offered at health facilities, and community-based screening will be offered through HSAs, with facility referral of HPV-positive women.

## Methods/design

### Aims and objectives

Our aim is to compare the effectiveness, acceptability, appropriateness, feasibility, and budget impact of integrating self-sampled HPV testing into FP services via clinics only versus including community-based screening.

Our specific objectives are as follows:
Compare the effectiveness of our two models on uptake of CCS and FP services among eligible women in the catchment areas of health facilities assigned to the two models. The effectiveness will be evaluated through analysis of an Endline Household Survey, which will be administered to randomly selected eligible women in the catchment areas of the health facilities at the end of project implementation.
We hypothesize that the proportion of eligible women who have received CCS services during the 12 months of project implementation will be higher among eligible women in the catchment areas of health facilities assigned to model 2 than in model 1.We hypothesize that the proportion of eligible women who have received FP services during the 12 months of project implementation will be higher among eligible women in the catchment areas of health facilities assigned to model 2 than in model 1.Assess the acceptability, appropriateness, and feasibility of the two models among key stakeholders, including providers, facility management teams, and clients. These implementation outcomes will be evaluated through analysis of mixed methods assessments, including use of quantitative tools (Acceptability-Appropriateness-Feasibility Tool, Client Exit Survey) as well as qualitative interviews with providers, facility management teams, and clients.
We hypothesize that both models will be viewed as acceptable and appropriate by health care providers, facility management teams, and clients.We hypothesize that both models will be feasible in a variety of health facilities in Malawi.Estimate the cost and budget impact of each model compared to the standard-of-care (VIA and cryotherapy). These outcomes will be evaluated through analysis of structured observations during time-and-motion studies, the Workload Assessment Tool, and cost expenditures during implementation of the study.
We hypothesize that both models will be more cost-effective than the current standard-of-care for the number of cervical cancer case averted.We hypothesize that model 1 will be more cost-effective than model 2.

### Design

This is a hybrid type 2 cluster randomized feasibility trial, with 16 health facilities in Malawi assigned to either a clinic-only or a clinic-and-community model for CCSPT. The study will take place over a period of 2.5 years, with a pre-implementation phase of 6 months, an implementation phase of 18 months, and a dissemination phase of 6 months (Fig. 1 and Table 1).

**Fig. 1 Fig1:**
[figure not shown]
Study phases, with activities listed for each phase. Italicized portion indicates site selection and implementation of the two models under the appropriate phases. *Due to constraints on community services offered at two matched facilities, these facilities were both assigned to model 1 and dropped from randomization scheme. Thus, 9 facilities will implement model 1 and 7 will implement model 2

**Table 1 Tab1:**
[figure not shown]
Work plan

The pre-implementation period will be used for obtaining ethical approvals, developing study-specific forms and procedures, selecting and randomizing facilities, and preparing facilities to offer the new services through equipment procurement, facility rehabilitation, and training. We will also complete time-and-motion evaluations and the first round of mixed methods assessments, involving interviews, focus groups, and surveys, to understand the baseline situation. During the implementation period, we will perform additional rounds of mixed methods assessments and collect routine service utilization data from each facility. Assessment details are provided in Table 2. Near the end of the implementation period, we will conduct an Endline Household Survey to assess uptake of CCSPT and FP services among women who live in the catchment areas of the health facilities. The Endline Household Survey will allow us to compare the screening and treatment rates of the clinic-only and the clinic-and-community model.

**Table 2 Tab2:** Descriptions of assessments, organized by objective

Assessment	Description	Participants	Sample size
Objective 1: Compare the proportion of eligible women who receive CCSPT and FP services in the catchment areas of health facilities assigned to the two models.			
Endline Household Survey	The survey covers prior and recent use of CCSPT and FP services.	Women residing in the catchment areas for the health facilities; must be aged 15–50 years and cannot have had their cervix removed.	8000 women
Objective 2: Assess the acceptability, appropriateness, and feasibility of the two models among key stakeholders, including providers, facility management teams, and clients			
Baseline Assessment Form	The form collects information about the facility’s capabilities for providing CCSPT and FP services.	Completed by research assistants, one form per facility	16 forms (one per facility)
Readiness Assessment Forms	The form includes Likert scale rankings for various parameters of the readiness of the facilities/health system to implement the two models. Participants will answer the survey in small groups, coming to consensus on each ranking.	District health management team members, health facility managers, and community stakeholders	16 forms (one per facility)
Manager and coordinator in-depth interviews (IDIs)	Interviews assess facility managers’ and coordinators’ attitudes towards project implementation.	Facility managers and coordinators currently working at one of the 16 facilities	24 participants (3 from Zomba and 3 from Lilongwe each, at 4 time points)
Provider and HSA focus group discussions (FGDs)	Focus group discussions address providers’ and HSAs’ attitudes towards project implementation, including barriers, facilitators, successes, and challenges.	Providers currently working at one of the 16 facilities; includes HSAs at facilities randomized to community model	16 FGDs, 2 FGDs per district (1 with providers, 1 with HSAs) at 4 time points
Acceptability-Appropriateness-Feasibility tool	This survey is completed by the officer-in-charge and 2 providers at 4 time points and asks participants to rank acceptability, appropriateness, and feasibility of project activities using Likert scales.	1 officer-in-charge and 2 providers from each of the 16 facilities at each time point	Up to 192 forms (up to 48 participants per 4 time points)
Client in-depth interviews (IDIs)	Interviews assess clients’ attitudes towards project implementation, including the acceptability of self-collection and of CCSPT/FP integration.	Clients who participated in cervical cancer screening via self-collection at one of the 16 facilities during the study period	32 participants (16 who were screened at facility and 16 who were screened in community)
Client Exit Survey	This survey includes a 5-point Likert scale to measure clients’ opinions and perceptions on quality of CCSPT and FP services.	Clients who accessed CCSPT and FP services at the facilities	Up to 2370 participants (790 participants each at 3 time points, with the number of participants interviewed per facility proportional to the number of FP clients at that facility)
Workload Assessment Tool	This survey asks providers and lab staff to self-assess their workload.	Providers, HSAs, and lab staff	240 participants (5 per facility per 3 time points)
Observation checklist	Structured observation of providers and lab staff to assess fidelity to project protocols.	Providers and lab staff	Up to 1152 checklists (one per facility per week)
Objective 3: Estimate the cost and budget impact of each model compared to the standard-of-care (VIA and cryotherapy).			
Service utilization data	De-identified information about CCSPT and FP services will be collected from clinic, HSA, and lab registers on a monthly basis.	Providers routinely record visit information in registers; research team members collect data	N/A (difficult to estimate projected number of clients for each register type)
Time and motion study	Research assistants will continuously observe providers, e.g., nurses and HSAs record the time spent on health care activities such as CCSPT and FP including non-health care activities	Providers, nurses, clinicians, HSAs, and lab staff	At least 1 staff member per facility from each category (e.g. provider, HSA, lab staff).
Client Exit Survey	This survey asks clients about the money and time expended accessing CCSPT and FP services at the clinics. It also includes the EQ-5D-3L survey to assess health-related quality-of-life for the cost impact analyses.	Facility clients	Up to 2370 participants (790 participants each at 3 time points, with the number of participants interviewed per facility proportional to the number of FP clients at that facility)

Throughout the implementation period, we will conduct weekly clinical supportive supervision visits and mentor the health facility providers, ensure appropriate logistical support, and assess providers’ fidelity to our protocols. Of note, while our study is ongoing, we will not restrict concomitant care or interventions at the study sites. Specifically, facilities are permitted to continue offering VIA and cryotherapy.

### Setting

This study will occur in two districts in Malawi: (1) Lilongwe in the Central Region and (2) Zomba in the Southern Region. It is unknown how cervical cancer incidence differs across the country, but regional variation in HIV prevalence suggests that there is likely variation in cervical cancer burden, since HIV infection greatly increases risk for persistent HPV infection and cervical cancer development [20]. HIV prevalence among women aged 15–49 is 10.8% nationally, 6.7% in the central region, and 15.7% in the southern region [21]. Without knowledge of how cervical cancer and HPV infection vary geographically, selecting districts from two different regions helps ensure better representativeness.

Malawi is a country of 18.1 million people in southeastern Africa. Gross domestic product (GDP) is $516 USD, among the lowest in the world [22]. Health care facilities in Malawi are operated by the Ministry of Health (MoH), the private for-profit sector, and the Christian Health Association of Malawi (CHAM), which is Christian-affiliated and heavily publicly subsidized [23]. In most facilities regardless of sector, service utilization data is recorded in standardized MoH registers. The MoH organizes regular surveillance of facility service utilization by having facilities submit monthly reporting forms to District Health Offices [23].

HSAs in Malawi comprise 30% of the health care workforce [23]. Originally, HSAs focused on immunizations and health education, but their role has since been expanded to clinical activities such as pediatric disease management, HIV testing, and FP provision [24]. HSAs typically deliver services in community outreach or village clinics, which are held in a given location anywhere from several times a week to once every few weeks. Some HSAs are utilized to provide basic care in health facilities or to provide home visits. The minimum qualifications for an HSA are a secondary school certificate and completion of a 12-week MoH-administered HSA training program [24].

In 2015, there were 130 public health facilities providing VIA and one providing Pap smear [3]. For treatment, 32 public facilities provided cryotherapy, though the machines were only functional at 22, and 11 offered thermal ablation. More sites have likely added thermal ablation since 2015, since thermal ablation was only introduced in the country in 2013 and added to the National Cervical Cancer Control Strategy in 2016 [13].

### Sample size calculations

Sample size calculations were based on the ability to detect a difference in service uptake through the Endline Household Survey. As noted earlier, only 26.5% of Malawian women had been screened at least once in their lifetime as of 2015 with use of VIA for primary screening [3], which is much lower than the targeted rate of 80% set at the onset of Malawi’s Cervical Cancer Control Program in 2004 [16]. We estimated that with the introduction of HPV self-sampling in our clinic-only arm, at least 40–50% of eligible women in our facility catchment areas will be screened during our 18 months of implementation. We then estimated that with the addition of HPV self-sampling in the community to reach rural women, we would be able to approach Malawi’s targeted rate of 80% of eligible women screened in our clinic + community arm. Based on data obtained from potential facilities in Lilongwe and Zomba, we also estimated an average cluster size of 8000 eligible women per health facility and a coefficient of variation of the cluster sizes of 0.35. Finally, we estimated that our intra-cluster correlation coefficient (ICC) will be between 0.12 and 0.19, based on other similar studies performed in Malawi, where the ICC ranged from 0.004 to 0.20 [25, 26]. With 16 randomized facilities (8 per arm), we initially estimated that we would have at least 80% power to detect a difference of at least 25–30% between our 2 arms, even if the proportion of women screened in the clinic-only arm is as low as 40%. For example, if the clinic-only arm found that 40% of women had been screened, we would have 80% power to detect a difference if the clinic + community arm had screened at least 75% of women in their catchment areas.

However, after performing site selection and randomization, we learned that the two central/district hospitals selected could not be assigned to model 2 as their HSAs did not perform community-based services. Therefore, we dropped these 2 hospitals from our sample size calculations and decreased our average cluster size to 3400 eligible women accordingly. With an ICC of 0.15 and coefficient of variation of cluster sizes of 0.35, we will have at least 83% power to detect of difference of at least 30% between our 2 arms (with 7 facilities in each arm), even if the proportion of women screened in the clinic-only arm is as low as 40%. All power calculations were calculated in R (Version 3.5.1, clusterPower package).

For the other study components, the sample size explanations are listed in Table 2.

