### Analysis plan

#### Endline Household Survey

Key outcomes from the Endline Household Survey include (1) the proportion of eligible women who have received CCS during the 18 months of study implementation, (2) the proportion of treatment-eligible women who received thermal ablation during the study period, and (3) the proportion of women aged 15–50 years who are using a modern FP method. These proportions will be calculated using descriptive statistics. Differences between the clinic-only and clinic-and-community models will be assessed via logistic regression, adjusted for district, facility size, and facility type. The regression model will account for health facility clustering, and analyses will be adjusted for the small number of clusters [28, 29].

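### The stated 83% power is a normal-approximation figure that omits the planned small-number-of-clusters adjustment; a t reference on 12 df gives about 75% at the same ICC.

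*Protocol article*

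**What the plan says.** The section on sample size calculations in the protocol article bases power on the Endline Household Survey. It first describes a design with 8 facilities per arm, with "an average cluster size of 8000 eligible women per health facility and a coefficient of variation of the cluster sizes of 0.35", both estimated from data on potential facilities in the two districts. On the ICC it states: "we estimated that our intra-cluster correlation coefficient (ICC) will be between 0.12 and 0.19".

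After the two central/district hospitals left the randomised comparison, the authors "decreased our average cluster size to 3400 eligible women accordingly". For this design, at an ICC of 0.15 and a CV still of 0.35, they state that "we will have at least 83% power to detect of difference of at least 30% between our 2 arms". The figure is given for seven clusters per arm and a clinic-only screening proportion down to 40%. The calculations used the R package clusterPower. The text mentions no small-sample correction, alpha or sidedness.

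The analysis plan for the Endline Household Survey specifies logistic regression "adjusted for district, facility size, and facility type", and then: "The regression model will account for health facility clustering, and analyses will be adjusted for the small number of clusters". The correction method is not named.

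**The concern.** Power is a property of the test that will be carried out. With 14 clusters, the usual small-sample corrections refer the arm effect to a t-type distribution on roughly the number of clusters minus the number of cluster-level parameters, or penalise it to a similar degree. The critical value on 12 df is 2.18, against 1.96 for the normal. With a signal of under three standard errors, that difference costs several points of power. If the 83% was obtained with 1.96, the sample size section and the analysis section describe different tests.

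This is the only power figure for the 14-facility comparison of the two models. A reader who accepts 83% expects a true 30-point gain to be missed about one time in six. If the miss rate is nearer one in four, a null result could be read as stronger evidence against community screening than it is, in a trial meant to inform national policy.

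A second, smaller point is that the CV of 0.35 was carried over unchanged although the mean cluster size more than halved when the hospitals left.

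**Working it through.** **Inputs from the section on sample size calculations:** p1 = 0.40, p2 = 0.70 (40% plus 30 points), m = 7 clusters per arm, n = 3400, ICC = 0.15, CV = 0.35; ICC planning range 0.12 to 0.19. **Assumed:** two-sided alpha 0.05.

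**Step 1. Reproduce the stated figure.**
- Design effect = 1 + ((CV² + 1)·n − 1)·ICC = 1 + ((0.1225 + 1)·3400 − 1)·0.15 = 573.3.
- Effective number per arm = 7·3400 / 573.3 = 41.5.
- SE = √[(0.40·0.60 + 0.70·0.30) / 41.5] = √(0.45 / 41.5) = 0.104.
- Difference / SE = 0.30 / 0.1041 = 2.88.
- Power with the normal value = Φ(2.88 − 1.96) = 82.2%. Multiplying the CV² term by (m − 1)/m gives 82.7%.

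The stated 83% is therefore reproduced to within a point, with a normal critical value.

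**Step 2. Change only the reference distribution.** Keep the SE and use a two-sided noncentral t with noncentrality 2.88.
- Two arms only: df = 2·(7 − 1) = 12, critical value 2.18, power 75.3%.
- Charging the planned covariates as well: district 1 df, facility size 1 df (if linear) and facility type 2 df (three types remain), so df = 12 − 4 = 8, critical value 2.31, power 71.4%. This takes the df away but credits no reduction in between-cluster variance.

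**Step 3. Repeat over the plan's ICC range (40% vs 70%).**

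| ICC | Difference / SE | Normal | t, 12 df | t, 8 df |
|---|---|---|---|---|
| 0.12 | 3.22 | 89.6% | 84.0% | 80.5% |
| 0.15 | 2.88 | 82.2% | 75.3% | 71.4% |
| 0.19 | 2.56 | 72.6% | 65.3% | 61.3% |

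**Step 4. Difference detectable with 80% power from 40% (t, 12 df).** Solving the same formula for p2 gives about 32 points at ICC 0.15 and about 35 points at ICC 0.19.

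**Step 5. Does the choice of cluster size drive the result?** The survey targets up to 8000 women over 16 catchments, about 500 each. Putting roughly 500 to 570 surveyed women per cluster in place of 3400 gives about 82% (normal) and 75% (t, 12 df) at ICC 0.15. With an ICC this large, cluster size hardly matters.

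**The case against.** **The arithmetic is not wrong.** The 83% follows from the stated inputs under a standard large-sample formula. This stands. The fault is a mismatch between the power calculation and the planned analysis, worth about 7 points at ICC 0.15 and 12 df.

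**The ICC is an explicit condition.** A reader might infer from the words at least that 83% is claimed over the whole range 0.12 to 0.19, and is refuted by 73% (normal) at 0.19. The sentence does not support this: it fixes the ICC at 0.15, and its minimum wording attaches to the size of the difference and to the clinic-only proportion. Nor would it be right to say that 83% can be reached only with a normal reference, because at ICC 0.12 the t reference on 12 df gives 84%. The range is a sensitivity display that the restatement should carry.

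**The correction is unnamed, and adjustment may help.** Facility type was the randomisation stratum and district is a plausible source of variation, so covariates could recover some between-cluster variance. The CV penalty also depends on the analysis: without it, as in an unweighted cluster-level analysis, 12 df at ICC 0.15 gives 80%. The 8-df figures are therefore a pessimistic case and not a property of the planned analysis. This objection narrows the finding but does not remove it, because even the no-penalty case falls below its own normal-based figure of 86%.

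**The expected effect is larger than 30 points.** The authors hope to approach 80% in the clinic-and-community arm. For 40% vs 80%, 12 df gives 96% at ICC 0.15 and 91% at 0.19; for 40% vs 75%, 89% and 80%. The shortfall thus sits near the 30-point minimum, but that minimum is what the power statement is about. At 50% vs 80%, also 30 points, 12 df at ICC 0.15 gives 79%.

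**The CV.** Treating 8000 as the exact mean of the 16 sites gives two hospitals of (16·8000 − 14·3400)/2 = 40,200 each, hence a 16-site CV of at least 1.52, and a reader might conclude that 0.35 is wrong. The documents do not support this. The 8000 and the 0.35 were planning estimates from potential facilities, and a 16-site CV says nothing about the 14 that remain. What is left is a reason to check the value.

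**Conclusion.** The point holds in a limited form. The power of at least 83% is a large-sample figure (82 to 83%) that leaves out the small-number-of-clusters adjustment to which the same article commits. On the article's inputs, and with two-sided alpha 0.05 assumed, a t reference on 12 df gives about 75% at ICC 0.15, so a true 30-point difference would be missed about one time in four (100 − 75 = 25%), not about one in six (100 − 83 = 17%). The 71% figure additionally assumes that four covariate df are spent with no gain in precision.

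All these figures assume that the CV of 0.35 holds for the 14 retained catchments and that the correction behaves like a t reference. The documents establish neither an error in that CV nor a need to change the covariate set. The design is not shown to be inadequate for the larger effects that the authors expect.

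**What to change.** In the section on sample size calculations:

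1. Restate power for the 14-facility comparison with a small-sample (t-type) reference consistent with the planned analysis, and state alpha and sidedness. On the present inputs and 12 df, the sentence would read along these lines: about 75% power for 40% vs 70% at an ICC of 0.15; 80% power needs a difference of about 32 points.
2. Show the figure over the plan's ICC range: about 84% at 0.12 and about 65% at 0.19, where 80% power needs about 35 points.
3. Recompute the CV from the 14 retained catchment sizes. Confirm 0.35, or replace it and rerun.

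The cost is a rerun and a rewritten sentence. No sites or women are added and the planned model stays as it is. The stated power becomes less favourable.
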